### Eligibility criteria

The inclusion and exclusion criteria are summarized in Table 1.

**TABLE 1 T1:** Eligibility criteria.

Inclusion criteria	
**Age**	21–65 years
**Chronicity**	More than 12 months post-injury at enrollment
**Injury type**	Traumatic or non-traumatic incomplete cervical SCI, neurological level C2 to C8
**AIS classification**	Grade C or D
**UEMS**	10 to 20 out of 25 on the more impaired side; lower bound 10 ensures sufficient voluntary activation for task training and elicitable MEPs, upper bound avoids ceiling effects.
**Grip strength**	MMT grade 3 or higher in finger flexors (C8 myotome) on at least one side.
**Hand function**	Able to transfer at least 1 block across the partition within 60 s on the more impaired side.
**Sitting tolerance**	Able to tolerate upright seated posture in own wheelchair for at least 1 continuous hour without symptomatic orthostatic hypotension or pressure-related discomfort requiring position change.
**Medical stability**	No acute medical complications
**Informed consent**	Able to provide written informed consent and comply with the study schedule
**Medications**	Stable regimen for 4 weeks prior, AND participant plus clinician agreement that dosage (baclofen, tizanidine, botulinum toxin) remains unchanged throughout the 12-week intervention; any change logged as protocol deviation
**Surgical clearance**	Cleared by neurosurgeon or orthopedic surgeon for participation in tSCS-based rehabilitation
Exclusion criteria	
**Seizure history**	History of seizures or epilepsy
**Implanted devices**	Intracranial metallic implants, cochlear implants, cardiac pacemakers, or other implanted electronic devices. Cervical spinal instrumentation (e.g., posterior rods, plates, or screws at C2 to T1) is not an exclusion for tSCS provided overlying skin is intact; participants with hardware directly beneath planned electrode sites will undergo low-intensity test stimulation during screening, and electrode placement will be shifted by one interspace if current distortion, focal discomfort, or unexpected motor thresholds are observed. Intracranial hardware remains an absolute exclusion for iTBS.
**Prior craniotomy**	Prior neurosurgical procedure involving craniotomy
**Pregnancy**	Currently pregnant or intending to become pregnant during the study period
**Psychiatric or cognitive**	Active psychiatric illness (eg, untreated major depression, psychosis) or cognitive impairment precluding informed consent

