### Randomization and allocation concealment

Participants will be randomized in a 1:1 ratio using a computer-generated, permuted block randomization schedule (block sizes of 4 and 6, randomly varied) stratified by AIS grade (C versus D) and baseline UEMS on the more impaired side (10–14 versus 15–20). The randomization schedule will be generated by an independent biostatistician at the Clinical Research & Innovation Office, Tan Tock Seng Hospital, with no direct involvement in participant recruitment or assessment, and stored in a secure, web-based centralized randomization system (REDCap Randomization module). Allocation concealment will be ensured by sequential, opaque, sealed envelopes accessible only to the unblinded intervention therapist.

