### Statistical analysis

All analyses will follow the intention-to-treat (ITT) principle, defined as all randomized participants who receive at least one treatment session and have at least one post-baseline assessment. Continuous variables will be summarized as mean and standard deviation (or median and interquartile range where appropriate). Between-group comparisons for the primary outcome (UEMS change from baseline to week 12) will be analyzed using a linear mixed-effects model with treatment group, time, and treatment-by-time interaction as fixed effects, stratification factors (AIS grade and baseline UEMS) as covariates, and participant as a random effect. An unstructured covariance matrix will be assumed for repeated measures.

Secondary continuous outcomes will be analyzed using analogous mixed-effects models. Effect sizes (Cohen d) and 95% confidence intervals will be reported for all between-group comparisons to support the planning of a future definitive trial. A per-protocol analysis (participants completing 20 or more of 24 sessions) will be conducted as a sensitivity analysis. Missing data will be handled within the mixed-effects framework under the assumption of missing at random (MAR). Feasibility outcomes will be reported descriptively against the pre-specified progression criteria. A sensitivity analysis excluding participants with antispasticity dose changes will be conducted for the Modified Tardieu Scale outcome. Safety outcomes will be tabulated by treatment group with frequencies and proportions. All analyses will be performed using R (version 4.3 or later), with statistical significance set at P < .05. All between-group efficacy comparisons (primary and secondary) will be reported as exploratory. The trial’s primary purpose is estimation of effect sizes, variability, and feasibility parameters for a definitive trial. Secondary functional and neurophysiological outcomes carry elevated Type I error risk due to multiple testing without correction and should be interpreted as hypothesis-generating only.

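### The mixed models name only a two-band UEMS stratum as baseline covariate and no own-baseline term for secondary outcomes, which costs some precision and, on one reading, misstates the UEMS standard error

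*Protocol article*

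**What the plan says.** All references are to the protocol article.

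- **Statistical analysis, primary outcome:** "Between-group comparisons for the primary outcome (UEMS change from baseline to week 12) will be analyzed using a linear mixed-effects model". Its fixed terms are arm, visit and their product, and it adds the "stratification factors (AIS grade and baseline UEMS) as covariates, and participant as a random effect". On covariance: "An unstructured covariance matrix will be assumed for repeated measures".
- **Statistical analysis, secondary outcomes:** "Secondary continuous outcomes will be analyzed using analogous mixed-effects models". No covariate specific to the outcome is named.
- **Randomization and allocation concealment:** allocation is "stratified by AIS grade (C versus D) and baseline UEMS on the more impaired side (10–14 versus 15–20"). The UEMS stratification factor therefore has two levels.
- **Table 1:** entry requires a UEMS of "10 to 20 out of 25 on the more impaired side".
- **Tables 2 and 3:** every efficacy measure is scheduled at week 0.

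The text does not say whether week 0 is one of the levels of time in the response, or whether change scores are the response.

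**The concern.** The trial exists mainly to supply effect sizes and variability for a definitive trial, from 12 participants per arm. A baseline value that has already been measured is the cheapest source of precision at that size. Read literally, the plan uses baseline UEMS only as two bands and gives the secondary outcomes no baseline covariate of their own.

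The two possible forms of the model also behave differently:

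- **Week 0 in the response.** AIS grade and UEMS band enter as main effects that are the same at every visit, so they drop out of a difference between visits. The model then takes no account of the stratified allocation, and its standard error is too large.
- **Change as the response.** The band does adjust, but only for the part of baseline UEMS that it captures. Secondary outcomes are adjusted for a UEMS band instead of for themselves.

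At stake are intervals wider than they need to be, and a UEMS standard error that does not match the true variability of the estimate. Both would pass into the planning of the next trial.

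**Working it through.** The protocol gives no power or precision figure on this point, so there is none to reproduce.

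**Inputs from the protocol:** 24 participants, 1:1 (Sample size); two-by-two strata with blocks of 4 and 6 (Randomization); entry UEMS 10–20 (Table 1); main visits at weeks 0, 12, 16 and 24 (Table 3); model terms (Statistical analysis).

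**Assumptions:** baseline-to-follow-up correlation ρ from 0.5 to 0.9; equal SD at baseline and follow-up; baseline UEMS uniform on 10–20; correlation 0.4 between a secondary outcome and UEMS.

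**Step 1: do the covariates cancel?** With week 0 in the response, the mean for group G at visit t is α + τ_t + δG + γ_tG + β₁·AIS + β₂·band. The between-group difference in change to week 12 is γ₁₂ − γ₀; β₁ and β₂ do not appear. In a simulated complete data set (24 participants, four visits, unstructured covariance), the contrast was −0.160 with SE 0.848, both with and without the two covariates. It equalled the raw difference in mean change. A baseline-constrained model on the same data gave SE 0.799.

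**Step 2: how much of baseline UEMS do the bands carry?** The variance of the 11 integers 10–20 is (11² − 1)/12 = 10. Within 10–14 it is (5² − 1)/12 = 2; within 15–20 it is (6² − 1)/12 = 2.92. The pooled within-band variance is (5 × 2 + 6 × 2.92)/11 = 2.5. The bands therefore carry 75% and leave 25%. Under truncated-normal shapes they carry about 60–68%.

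**Step 3: large-sample benchmark without stratification.** Up to a common factor, the variance of unadjusted change is 2σ²(1 − ρ) and of the baseline-adjusted estimate σ²(1 − ρ²). Their ratio is (1 + ρ)/2 = 0.75, 0.85, 0.90 and 0.95 at ρ = 0.5, 0.7, 0.8 and 0.9. The SE of unadjusted change is thus 15%, 8%, 5% and 3% larger.

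**Step 4: the same comparison under stratified allocation (simulation).**

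| ρ | UEMS, week 0 in response: interval vs continuous baseline | UEMS, change with band: SE vs continuous baseline | Secondary, change with band: interval vs own baseline |
|---|---|---|---|
| 0.5 | 14% wider | 3% larger | 11% wider |
| 0.7 | 7% wider | 1.5% larger | 4% wider |
| 0.8 | 4% wider | 0.6% larger | 2% wider |
| 0.9 | 1% wider | 0% | 0% |

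The first and third comparisons use 24 participants and the protocol's strata and blocks. The second uses 20 evaluable participants balanced within UEMS band.

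For UEMS at ρ = 0.5 with 24 participants, in units of the baseline SD:
- Unadjusted change: true SD of the estimate 0.371, average reported SE 0.406, coverage of the 95% interval 96.9%.
- Continuous baseline plus AIS grade: true SD 0.351, reported SE 0.355, coverage 95.4%.

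**Step 5: chance imbalance in UEMS.** With simple randomization the expected absolute difference is √(2/12) × √(2/π) = 0.408 × 0.798 = 0.33 SD. If the bands are balanced and 25% of the variance lies within them, it is 0.33 × √0.25 ≈ 0.16 SD. A change analysis passes on only the share (1 − ρ).

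**The case against.** **The wording may mean something better.** The UEMS covariate could be the continuous score, and an analogous secondary model could put each outcome's own baseline in place of UEMS. Covariate coding is often left to the analysis plan. The ambiguity is real. But the section does fix the fixed effects, covariates, random effect and covariance, and it calls these covariates the stratification factors. The Randomization section defines the UEMS factor as "baseline UEMS on the more impaired side (10–14 versus 15–20"). Two bands is the literal reading, and what the text fixes can be improved.

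**Stratification already protects the primary outcome.** With 20 evaluable participants, the true SD of the UEMS estimate was 1.281 for unadjusted change and 1.274 with continuous baseline at ρ = 0.5. At ρ = 0.7 it was 1.034 and 1.049. This stands for the true variability. It does not rescue the reported standard error when week 0 is in the response, because that model does not credit the stratification (0.406 reported against 0.371 true in step 4).

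**Little depends on it.** All efficacy comparisons are labelled exploratory, and no progression criterion uses an efficacy result. This stands and limits the weight of the point.

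**Stronger readings that a reader might infer, and that the documents do not support:**
- *That secondary baselines go unused.* Under change scores, or with week 0 in the response, baseline is used by subtraction. Only a covariate is missing.
- *That secondary outcomes would be modelled as raw follow-up values with no baseline.* The loss would then be large, but the model they copy is framed as change from baseline.
- *That UEMS power would rise from 65% to 77%* (true difference of 1 SD of change, ρ = 0.5), *or that a 0.33 SD imbalance should be expected.* Both figures assume unstratified allocation, and the protocol stratifies on UEMS.
- *That the analysis is biased or invalid.* The change contrast is unbiased over randomization.

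**Conclusion.** The point holds as one of efficiency and of correctly stated standard errors. Its size depends on which model is fitted, and the protocol does not settle that.

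- **UEMS, week 0 in the response:** reported intervals about 1–14% wider than with continuous baseline, and conservative.
- **UEMS, change with the band:** a loss of about 0–3%, which is negligible.
- **Secondary outcomes, change with the band:** intervals about 0–11% wider than with own-baseline adjustment.

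In each case the larger figure belongs to ρ = 0.5, and the loss all but disappears at ρ = 0.9. The figures rest on assumed values of ρ, a uniform baseline UEMS and, for secondary outcomes, a 0.4 correlation with UEMS. The documents give none of these. The change is worth making because it costs almost nothing, not because the planned analysis would mislead.

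**What to change.** In the Statistical analysis section:

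1. State the response: post-baseline values at weeks 12, 16 and 24 (for each secondary outcome, its own scheduled post-baseline visits).
2. In the primary model, enter baseline UEMS as a continuous covariate, on the same scale as the endpoint (one side or bilateral), with a baseline-by-time interaction, plus AIS grade.
3. Replace the reference to analogous models with a sentence saying that each continuous secondary outcome is adjusted for its own week-0 value plus the stratification factors.
4. Alternatively, use a baseline-constrained longitudinal model, with week 0 in the response and equal arm means at baseline.

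The cost is a change of wording and a few model parameters, up to three per model if baseline-by-time is included. With 20 to 24 participants that is not quite free, and nothing is gained if ρ is near 0.9. No new data are needed, and the article states that no participant had been enrolled when it was prepared.

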**Concurrent neurological disease**	Progressive or degenerative neurological condition (eg, multiple sclerosis, motor neuron disease)
**Concurrent trials**	Participation in another interventional rehabilitation or neurostimulation trial
**Skin integrity**	Skin lesions or breakdown at electrode placement sites (scalp or posterior cervical spine)
**Cortical excitability medications**	Medications known to alter cortical excitability (eg, antiepileptic drugs, high-dose benzodiazepines) that cannot be stabilized for at least 2 weeks prior to enrollment
**Severe spasticity**	Modified Tardieu Scale muscle reaction grade 4 (unfatigable clonus > 10 s) at elbow or wrist flexors on the more impaired side, or spasticity judged by the treating physician as unresponsive to optimized pharmacological management.

AIS, American Spinal Injury Association Impairment Scale; UEMS, Upper Extremity Motor Score; SCI, spinal cord injury; tSCS, transcutaneous spinal cord stimulation.

Restriction to motor-incomplete injuries is mechanistic. Convergent neuromodulation relies on residual corticospinal substrate for STDP-driven strengthening; AIS A and motor-absent AIS B injuries cannot reliably engage this pathway and would produce UEMS floor effects. Extension to AIS B participants with preserved transcranial MEPs is planned for the confirmatory trial.

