#### Sample size

This is an exploratory pilot trial, and the sample size of 24 participants (12 per group) is based primarily on feasibility considerations and is consistent with recommendations for pilot studies in neuromodulation and SCI rehabilitation (Julious, 2005). This sample size is sufficient to estimate the standard deviation of the primary outcome, assess feasibility parameters, and generate preliminary effect size estimates with reasonable precision to inform the power calculation for a subsequent confirmatory trial. Assuming 20% attrition, we aim to enroll 24 participants to ensure at least 10 evaluable participants per arm. This is consistent with sample sizes in comparable neuromodulation pilot trials in SCI (Feng et al., 2023; Gharooni et al., 2018; Lin et al., 2023).

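### Planning inputs for the definitive trial are better reported in UEMS points with their SDs; any standardised effect should be Hedges g with a named SD, not plain Cohen d

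*Protocol article*

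**What the plan says.** The Statistical analysis section of the protocol article names the effect measure and its use in one sentence: "Effect sizes (Cohen d) and 95% confidence intervals will be reported for all between-group comparisons to support the planning of a future definitive trial". The same section says that the trial's "primary purpose is estimation of effect sizes, variability, and feasibility parameters for a definitive trial". The Sample size section ties these estimates to the power calculation of the confirmatory trial, and the Conclusion says they will feed directly into its powering.

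The primary comparison is the UEMS change from baseline to week 12. It comes from a linear mixed model with group, time and their interaction, the stratification factors as covariates, a participant random effect and an unstructured covariance. The article does not say which SD standardises d in this model. It neither mentions nor rules out a small-sample correction.

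On numbers, "the sample size of 24 participants (12 per group) is based primarily on feasibility considerations", and the section adds: "Assuming 20% attrition, we aim to enroll 24 participants to ensure at least 10 evaluable participants per arm".

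**The concern.** Two features of plain Cohen d make it a weak planning input here.

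First, the sample SD in its denominator makes d too large on average, and at 10 to 12 per arm this is measurable. The corrected statistic has its own name, Hedges g, so writing Cohen d ordinarily means no correction. The Discussion asks readers to take the pilot effect sizes as a lower bound on achievable benefit. Its reason is session density, which does nothing about the direction of this bias.

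Second, a repeated-measures model offers several candidate SDs: baseline, week 12, change score, or residual after baseline adjustment. One difference in UEMS points gives a different d with each. A required sample size varies with 1/d², so whoever plans the next trial has to know which SD was used and whether it fits that trial's analysis.

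What is at stake is the usability of the pilot's main output. No conclusion within the pilot depends on it.

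**Working it through.** **Inputs from the article.** 12 per arm randomised, so df = 22; at least 10 per arm evaluable, so df = 18; significance level 0.05. The plan's own figure is roughly reproduced: 12 × 0.8 = 9.6, or about 10 per arm.

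**Assumptions (not in the article).** Two-sided test; 80% power for the next trial; true d of 0.3, 0.5 and 0.8 as illustrations; equal SDs at baseline and week 12, with correlation r, in step 5.

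**1. Size of the bias.** The exact factor is J = Γ(df/2) / [√(df/2) · Γ((df−1)/2)], and the expected value of d is true d / J.

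| Per arm | df | J | Average excess, 1/J − 1 | Expected d if true d = 0.5 |
|---|---|---|---|---|
| 12 | 22 | 0.9655 | 3.6% | 0.518 |
| 10 | 18 | 0.9576 | 4.4% | 0.522 |

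**2. Effect on a sample size computed at the expected d.** With the noncentral t, true d = 0.5 needs 64 per arm. Using 0.518 gives 60 and using 0.522 gives 59. True power is then 77.5% and 76.8%. The normal approximation gives 63, 59 and 58 with the same power to one decimal. The loss is about 2.5 to 3.2 percentage points.

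**3. The bias beside the noise.** The half-width of the 95% CI is 1.96 · √(2/n + d²/(4n)). At d = 0.5:
- n = 12: 1.96 · √(0.1667 + 0.0052) = 0.81, an interval from −0.31 to 1.31
- n = 10: 1.96 · √(0.2000 + 0.00625) = 0.89, an interval from −0.39 to 1.39

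The bias is 0.018 and 0.022, so the half-width is at least 40 times larger. Over true d from 0.3 to 0.8 it is at least 25 times larger.

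**4. Does correction change the risk of undersizing?** In 400,000 simulated pilots per setting (true d of 0.5 and 0.8), plain d exceeded the true d in 50.5% to 51.0% of them. Hedges g did so in 48.0% to 48.8%. The difference is slight. Correction does improve accuracy: at true d = 0.5, mean squared error falls from 0.190 to 0.177 (12 per arm, 6.9%) and from 0.234 to 0.214 (10 per arm, 8.5%).

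**5. Effect of the dividing SD.** If both visits have SD s, the change SD is s · √(2(1 − r)) and the baseline-adjusted SD is s · √(1 − r²). Relative to d on the raw SD:

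| r | d on change SD | d on baseline-adjusted SD |
|---|---|---|
| 0.3 | 0.85 | 1.05 |
| 0.5 | 1.00 | 1.15 |
| 0.7 | 1.29 | 1.40 |
| 0.8 | 1.58 | 1.67 |
| 0.9 | 2.24 | 2.29 |

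This matters far more than the 4% bias, but its direction is not fixed. If a d scaled to a small SD is used for a trial whose analysis has a larger SD, that trial is undersized. The reverse oversizes it. A d on the change SD, used for a change-score analysis, is correct.

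**The case against.** The strongest case on the other side has three parts.

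- **Much of what is needed is already planned.** The article will estimate the SD of the primary outcome, report confidence intervals, and fit a model that yields a difference in UEMS points and the covariance between visits. The Hypotheses section gives a raw target of 2 points. A route to sample size without d is therefore open, and the wording "to support the planning of a future definitive trial" does not commit anyone to inserting the point estimate of d. This stands, and it limits the weight of the point. It does not make plain d the better measure to name.
- **The divisor is a detail an article may leave to the analysis plan.** This also stands: the unnamed SD alone would be no finding. What can be judged is the stated choice of Cohen d as the measure offered for planning.
- **The bias is trivial beside the imprecision.** Steps 3 and 4 confirm this.

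Two stronger readings are tempting. A reader might infer that the next trial would be sized too small. The documents do not support that: over- and underestimation of d are almost equally likely, with or without correction, and an SD mismatch can act either way.

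A reader might also infer that d cannot carry over because entry is limited to "10 to 20 out of 25 on the more impaired side" while "Extension to AIS B participants with preserved transcranial MEPs is planned for the confirmatory trial". That does not hold as an argument for raw units. The SD in UEMS points comes from the same restricted sample, and the planned extension does not say that the UEMS window will change.

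**Conclusion.** The point holds as a minor improvement to a stated method. Cohen d as ordinarily defined is biased upwards by 3.6% (12 per arm) to 4.4% (10 per arm), and in this mixed model its value is ambiguous until an SD is named. The bias figures follow exactly from the arm sizes, under normal outcomes with equal variances and a pooled two-group SD. They rest on reading Cohen d as uncorrected, which is the usual meaning but is not spelled out. The power figures assume 80% power, a two-sided test and a true d of 0.5. The SD ratios assume equal SDs at the two visits and a correlation that the article does not give.

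Nothing here shows that the confirmatory trial would be undersized. The pilot's wide interval is the dominant uncertainty, and the correction does not remove it.

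**What to change.** In the Statistical analysis section, replace the sentence on Cohen d with wording along these lines: for each between-group comparison, report the adjusted difference in the outcome's own units with its 95% CI. For the UEMS, also report the baseline SD, the week-12 SD and the baseline to week-12 correlation, and name these quantities, with the difference in UEMS points, as the inputs to the confirmatory power calculation. If a standardised effect is also given, use Hedges g and state the SD that divides it, matched to the analysis planned for the next trial. No single divisor needs to be imposed on every outcome.

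The cost is a sentence or two of wording. No new data are needed, and the article's Results section says that no participants had been enrolled when it was prepared. Reported standardised effects will be about 4% smaller.
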